#### *Physical condition and activity*

To measure maximal oxygen consumption (VO_2_max) a maximal exercise test will be performed.[44] In addition to the determination of VO_2_max, carbon dioxide production, heart rate, respiratory quotient, and ventilation will be measured. Patients will cycle with an increased workload of 10 Watt/min for women and 20 Watt/min for men. Patients will be verbally encouraged to perform maximally until exhaustion.

Daily activity will be measured during two weeks using an actometer.[45] The actometer used is a motion-sensing device, worn around the ankle, which can register and quantify human physical activity. The actometer has a piezoelectric sensor that is sensitive in three directions. Accelerations of the built-in sensor larger than a predefined threshold are considered as activity and are stored in an internal memory every five minutes. A general physical activity score expressed in the average number of accelerations per 5-min period will be provided for the whole measurement period. Actometer testing is part of the standard care if patients are referred for CBT. To assess the effect of the maximal exercise test on the daily activity of patients, they will wear an actometer for an additional five days after the maximal exercise test.

Finally, participants will score their physical activity level long before cancer diagnosis on a 10 point numeric rating scale.

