**Methods/design:**

Fifty seven severely fatigued and 21 non-fatigued cancer survivors will be recruited from the Radboud University Nijmegen Medical Centre. Participants should have completed treatment of a malignant, solid tumour minimal one year earlier and should have no evidence of disease recurrence. Severely fatigued patients are randomly assigned to either the intervention condition (cognitive behaviour therapy) or the waiting list condition (start cognitive behaviour therapy after 6 months). All participants are assessed at baseline and the severely fatigued patients also after 6 months follow-up (at the end of cognitive behaviour therapy or waiting list). Primary outcome measures are fatigue severity, central and peripheral fatigue, brain morphology and function, and physical condition and activity.

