### Physical condition and activity

Despite the fact that current cancer treatments are increasingly efficacious for improving survival, they are toxic in numerous ways. Therefore, many cancer patients are forced to decrease their physical activity, possibly leading to physical deconditioning. Physical activity levels were significantly reduced after diagnosis in a study of 812 breast cancer patients.[37] It may be hypothesized that compared to non-fatigued cancer survivors, PCF patients have an impaired physical condition due to decreased physical activity after cancer treatment.

In a previous study comparing physical condition in a group of 20 CFS patients and 20 matched non-fatigued sedentary controls, physical condition did not significantly differ between both groups. Although as a clinical syndrome CFS and PCF show strong similarities, in PCF a clear precipitating moment can be identified that provoked fatigue, namely the diagnosis of cancer and its subsequent treatment. In contrast to PCF, not always a precipitating factor can be identified in CFS. Therefore, studies on physical condition, specifically in cancer survivors, are needed to investigate the physiology of PCF.

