### Study population

Patients who have been curatively treated for cancer and finished treatment at least one year before, will be asked by their physician to fill out the Checklist Individual Strength (CIS),[38] RAND-36,[39] Beck Depression Inventory for Primary Care (BDI-pc),[40] and some additional demographic and medical questions during their control-visits. Based on the scores of the fatigue severity subscale of the CIS (CIS-fatigue), patients with a cut-off score of ≥35 will be classified as severely fatigued. Severely fatigued patients, who are referred to the Expert Centre for Chronic Fatigue of the RUNMC and who met the in- and exclusion criteria of the study (Table 1), will be informed by their treating psychologist about the study. If the patients agree to be further informed about the study, the researcher will inform the patients extensively about the study and will ask for participation. Severely fatigued patients will be matched with non-fatigued patients with respect to age, sex, and previous cancer treatment (Figure 1). A total number of 57 severely fatigued and 21 non-fatigued cancer survivors will be included (see power calculation).

**Table 1 T1:** Inclusion and exclusion criteria

**Inclusion criteria**	(1) Age between 19 and 65 years
	(2) Age at disease onset minimal 18 years
	(3) Treated for a malignant, solid tumour
	(4) Completion of treatment for cancer minimal 1 year ago (single treatment modality surgery/ current hormonal therapy permitted)
	(5) Disease-free, as defined by the absence of somatic disease activity parameters
**Exclusion criteria**	(1) Physical comorbidity that could explain the fatigue
	(2) Current psychological or psychiatric treatment
	(3) Brain tumour in the past
	(4) Contra-indication for MR examinations (e.g. claustrophobia)
	(5) Treatment with anti-depressive drugs, anti-epileptic drugs, or benzodiazepines
	(6) Insufficient command of the Dutch language to fill out questionnaires

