### Statistical analysis

Independent samples *t* tests will be performed testing baseline differences in primary and secondary outcome measures between fatigued and non-fatigued cancer survivors. Baseline differences between the therapy and waiting list condition are entered as covariates in further analyses. A paired *t* test will be performed to test whether differences can be observed within the therapy or waiting list condition from baseline to follow-up. Differences between the therapy and waiting list group on the change in outcome measures from baseline to 6 months later will be calculated with analyses of covariance (ANCOVA).

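### VO2max is compared between fatigued and non-fatigued survivors by an unadjusted t test; a prespecified ANCOVA with age, sex and body mass would be a cheap improvement

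*Protocol article*

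**What the plan says.** All references are to the protocol article.

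- **Status of the outcome.** The abstract (Methods/design) states: "Primary outcome measures are fatigue severity, central and peripheral fatigue, brain morphology and function, and physical condition and activity". Under Outcome measures, Physical condition and activity, the cardiopulmonary measure is VO2max: "To measure maximal oxygen consumption (VO_2_max) a maximal exercise test will be performed". No unit is given.
- **Hypothesis.** The Background section on physical condition and activity puts forward that, "compared to non-fatigued cancer survivors, PCF patients have an impaired physical condition due to decreased physical activity after cancer treatment".
- **Control group.** Study population: "Severely fatigued patients will be matched with non-fatigued patients with respect to age, sex, and previous cancer treatment". Body mass, height and BMI are not matching factors and are not mentioned elsewhere in the article.
- **Test.** Statistical analysis: independent samples t "tests will be performed testing baseline differences in primary and secondary outcome measures between fatigued and non-fatigued cancer survivors".
- **Covariates.** The same section adds: "Baseline differences between the therapy and waiting list condition are entered as covariates in further analyses". This rule concerns the two randomised arms. It does not reach the comparison of fatigued with non-fatigued survivors.
- **Rival explanations.** The section on fatigue and psychosocial measures adds a self-efficacy questionnaire as a possible explanation of a VO2max gap between these groups. No other explanation is planned for.

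**The concern.** The comparison that addresses deconditioning is observational. A t test without covariates relies on the design to make the groups alike, and here the design controls three factors. Two of them, age and sex, are strong determinants of VO2max. Matching brings their group means together, but their spread within each group stays in the error term unless the model includes them. Body size, a third determinant, is neither matched nor modelled.

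Two things are at stake. The first is precision: the control group is only about 20 people, and the test gives up precision that an adjusted analysis would recover. The second is interpretation. If fatigued survivors happened to be heavier, absolute uptake would make them look fitter than they are, while uptake per kg would make them look less fit at the same absolute uptake. With no adjusted analysis named for this comparison, the answer on deconditioning could depend on which scale is reported.

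**Working it through.** **Is there a stated figure to reproduce?** Not for VO2max. The Power calculation section says that 20 non-fatigued patients are sufficient but gives no effect size, SD, alpha or power for this comparison. Its only power figure concerns CIS-fatigue in the randomised arms: at least 80% with 30 v 10 patients and response of 67% v 10%. At an assumed two-sided alpha of 0.05, that gives 95.2% by a z test for two proportions and 89.0% by Fisher's exact test. The stated bound holds and has no bearing on this point.

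**Inputs from the article**
- Planned sizes: 57 fatigued and 21 non-fatigued (Study population).
- Technically insufficient measurements: 5% (Power calculation).
- Usable at baseline: 57 × 0.95 = 54.15, about 54; 21 × 0.95 = 19.95, about 20.

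**Assumed inputs (the article gives none of these)**
- Two-sided alpha 0.05.
- Share R² of the within-group variance of VO2max explained by age, sex and body mass together: 10% to 50%.
- For the bias illustrations: a correlation of 0.2 to 0.6 between absolute VO2max and body mass, and a group difference in mass of 0.2 to 0.5 SD.

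**Step 1. Planned test.** For the two-sample t test, the noncentrality is d / √(1/54 + 1/20) = d / 0.262, with 54 + 20 − 2 = 72 degrees of freedom. Solving for 80% power gives d = 0.743 SD.

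**Step 2. Adjusted test.** Adjustment shrinks the residual SD by √(1 − R²), so the detectable difference, in raw SD units, is 0.743 × √(1 − R²).

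| R² (assumed) | √(1 − R²) | Detectable difference | Power at d = 0.743 |
|---|---|---|---|
| 0 (t test) | 1.000 | 0.74 SD | 80% |
| 10% | 0.949 | 0.71 SD | 84% |
| 30% | 0.837 | 0.62 SD | 92% |
| 50% | 0.707 | 0.53 SD | 98% |

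Three covariates cost three degrees of freedom (72 to 69), which leaves the figures unchanged at this rounding. The table assumes that the groups are balanced on the covariates; imbalance in body mass would reduce the gain.

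**Step 3. Direction of a possible bias, absolute scale.** With no true difference at equal mass, the spurious difference is the correlation times the mass difference in SD units. Its range is 0.2 × 0.2 = 0.04 SD to 0.6 × 0.5 = 0.30 SD, in favour of the heavier group. With 54 v 20, a nominal 5% test then rejects in 5.3% to 20.5% of trials.

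**Step 4. Direction of a possible bias, per-kg scale.** Take equal absolute uptake of 2.0 L/min at 80 kg v 75 kg (all assumed). Then 2000/80 = 25.0 and 2000/75 = 26.7 mL/kg/min, a ratio of 75/80 = 0.9375, so the heavier group is 6.25% lower. Dividing by body mass therefore does not remove the dependence on size; it changes its sign.

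Steps 3 and 4 show direction only. Nothing in the article shows that the groups differ in mass.

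**The case against.** The strongest objection is that silence is being read as a decision. The article gives no unit for VO2max, and the planned t test would fit a per-kg value as well as an absolute one. Unit, scaling and recording of weight are details that an article commonly leaves to the full protocol, which is not shown. This stands: a reader might infer that the trial will analyse unscaled VO2max, but the text does not say so, and the missing unit is not itself a fault.

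Second, every bias figure rests on assumed values, and the low end, 5.3% instead of 5%, is practically nothing. Nor is a per-kg difference at equal absolute uptake plainly a false positive, because it is a real difference in capacity per kg. This also stands. A reader might conclude that the result on deconditioning will be wrong; the documents support only that it could depend on the scale.

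Third, weight gain may lie on the path from inactivity to poorer condition, in which case adjustment removes part of the effect of interest. This is a fair caution and shapes the fix, but it is a reason to show both analyses rather than to omit the adjusted one.

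Fourth, matching on age and sex already removes part of any body-size difference between the groups, and the randomised comparison concerns change within patients, where body size matters much less. Both are correct and limit the scope.

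The objections leave the choice of test untouched. The article does name the method for this comparison, and on either scale it is the weaker one.

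**Conclusion.** The point holds in a limited form. For a non-randomised comparison in a primary outcome domain, the plan specifies a t test without covariates on an outcome that depends on age, sex and body size, in groups matched only "with respect to age, sex, and previous cancer treatment". The loss is mainly precision. If those covariates explain 10% to 50% of the within-group variance, the detectable difference with 54 v 20 falls from 0.74 SD to about 0.71 to 0.53 SD. That range is an assumption, since the article gives no variance for VO2max. Bias from body mass is possible and its sign depends on the scale, but it is not documented, and no rate of false conclusions can be attributed to the plan. The randomised six-month comparison is little affected. This is a cheap improvement of minor to moderate weight, not an error that invalidates the comparison.

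**What to change.** For VO2max, replace the baseline t test between fatigued and non-fatigued survivors with a prespecified ANCOVA of log VO2max on group, with age, sex and log body mass as covariates. Weigh participants at the existing exercise visit. Report unadjusted absolute and per-kg means alongside, because body mass may lie on the causal path, and state the unit of each. For the randomised comparison, keep the planned ANCOVA and use the same VO2max scale at both visits.

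The cost is one weighing per exercise test and a sentence or two in the analysis plan. The downside, that adjustment may remove an effect acting through weight gain, is met by showing the unadjusted values.

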#### *Fatigue and psychosocial measures*

Fatigued severity will be measured using the CIS-fatigue (8 items, 7-points Likert Scale, severity range from 8 to 56).[38] High scores indicate a high level of fatigue. This questionnaire has excellent psychometric properties, including good reliability and discriminative validity.[46] Simultaneously to the actometer measurements, daily observed fatigue (DOF) will be measured with the Self-Observation List (4 times a day, 4-point scale)[47] two weeks prior and five days subsequent to the maximal exercise test. This instrument gives the actual level of daily fatigue. In this way, the relation between actual fatigue levels and the (neuro)physiological measures can be accessed directly.

To examine whether self-efficacy (SE) regarding the maximal exercise test could be an explanation for possible discrepancies in VO_2_max between fatigued and non-fatigued participants, SE regarding the maximal exercise test will be measured using a task-specific SE questionnaire. This questionnaire consists of 9 questions concerning sense of control (each item scored on a 4 point numeric scale, total score range from 9 to 36) and was adapted from the self-efficacy scale (SES)[48] The SES measures the perceived level of control over fatigue, whereas the task-specific SE questionnaire used in this study measures the sense of control regarding the test. A higher score indicates a higher sense of control regarding the maximal exercise test.

To assess whether environmental factors, like social support (SS) for exercise, may influence physical activity behaviour, SS will be investigated using the shortened van Sonderen SS Inventory (SSL).[49] The SSL is divided into the SSL-I (amount of SS, 8 questions, score range from 8 to 32), the SSL-D (discrepancy between the amount of SS and the desired amount of SS, 8 questions, score range from 0 to 32), and the SSL-N (negative interactions, unsupportive behaviour, 7 questions, score range from 7 to 28). A higher score indicates a higher amount of SS, discrepancy, or negative interactions.

### Statistical analysis

Independent samples *t* tests will be performed testing baseline differences in primary and secondary outcome measures between fatigued and non-fatigued cancer survivors. Baseline differences between the therapy and waiting list condition are entered as covariates in further analyses. A paired *t* test will be performed to test whether differences can be observed within the therapy or waiting list condition from baseline to follow-up. Differences between the therapy and waiting list group on the change in outcome measures from baseline to 6 months later will be calculated with analyses of covariance (ANCOVA).

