### Power calculation

From previous studies in patients with CFS compared to healthy controls we know that groups of at least 10, preferably 20 patients per condition are sufficient to detect significant differences in (neuro)physiological parameters measured with sEMG, MRI, and exercise testing.[21,28,50,51] To identify (neuro)physiological characteristics of fatigue, a comparison of baseline measurements with an age, sex, and previous cancer treatment matched group of 20 non-fatigued patients is sufficient. Fifty seven severely fatigued patients are needed to measure a change in (neuro)physiological factors due to CBT. As depicted in Figure 1, we assume that 5% of the measurements will yield technically insufficient data and 20% of the fatigued patients will drop-out from the study (14% drop-out due to failure to complete CBT or the follow-up measurements and 6% due to cancer recurrence during or after CBT or waiting list). Assuming that about two third of the patients who complete CBT will have a clinically significant response to CBT, defined as a CIS-fatigue score of less than 35 points, there will be 20 responding patients, 10 non-responding patients, and 10 untreated patients. Based on 30 patients in the CBT condition and 10 patients in the waiting list condition and assuming that the success rate of CBT is about 67% and the chance to recover spontaneously in the waiting list condition is maximally 10%, the power of the study to demonstrate a significantly greater decrease in CIS-fatigue score in patients in the intervention condition than in patients in the waiting list condition will be at least 80%.

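### The fatigued v non-fatigued baseline comparison is matched on age, sex and previous treatment, but the planned independent-samples t tests ignore those factors and so may be needlessly imprecise

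*Protocol article*

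**What the plan says.** Under Study population, the article fixes the matching: "Severely fatigued patients will be matched with non-fatigued patients with respect to age, sex, and previous cancer treatment". The Power calculation section repeats it: "a comparison of baseline measurements with an age, sex, and previous cancer treatment matched group of 20 non-fatigued patients is sufficient". It does not say whether individual pairs or sets are formed or whether the groups are balanced as a whole; the second wording reads more like group matching.

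The group sizes are given under Study population: "A total number of 57 severely fatigued and 21 non-fatigued cancer survivors will be included (see power calculation").

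The Statistical analysis section names an independent-samples t test for the baseline comparison of fatigued and non-fatigued survivors ("tests will be performed testing baseline differences in primary and secondary outcome measures between fatigued and non-fatigued cancer survivors"). The only covariates it mentions concern the randomised arms: "Baseline differences between the therapy and waiting list condition are entered as covariates in further analyses". No pairing, stratification or adjustment for age, sex or previous treatment is named for the matched comparison.

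**The concern.** Matching makes the two groups alike on the matching factors, so those factors contribute little to the chance variation of the difference in means. An independent-samples t test does not use this. It estimates its standard error from the whole within-group variance, including the part due to age, sex and treatment. The reported standard error then exceeds the true one, the confidence interval is too wide and a real difference is easier to miss. This holds for individual and for group matching.

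The comparison serves a stated aim, to identify (neuro)physiological characteristics of fatigue, and it has about 20 evaluable controls. Its size is justified only by experience in chronic fatigue syndrome that "groups of at least 10, preferably 20 patients per condition are sufficient to detect significant differences in (neuro)physiological parameters", without an effect size, SD or power. Avoidable noise is therefore worth removing.

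A second gap is that 57 and 21 patients cannot be fully paired one to one. Matching may leave some imbalance, and the planned test does nothing about it.

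**Working it through.** **Inputs from the article.** 57 fatigued and 21 non-fatigued patients; 20 controls needed; technical loss of 5% ("we assume that 5% of the measurements will yield technically insufficient data").

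**The plan's own figure.** 20/(1 - 0.05) = 21.05, against 21 stated, so the control group size is reproduced. Evaluable at baseline: 57 x 0.95 = 54.15 and 21 x 0.95 = 19.95, that is 54 v 20.

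**Assumed, because the article gives no value.** Two-sided alpha 0.05; a true difference of 0.6 SD; R2, the share of outcome variance explained by the matching factors, from 0 to 0.5; the same effect of the factors in both groups.

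**Standard errors.**
- Used by the t test: SD x sqrt(1/n1 + 1/n2) = SD x sqrt(1/54 + 1/20) = 0.262 SD.
- True value when the groups are balanced: 0.262 x sqrt(1 - R2). At R2 = 0.4 this is 0.262 x sqrt(0.6) = 0.203 SD.
- Ratio: 1/sqrt(1 - R2).

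**Type I error and power** (simulation of 54 v 20, covariate exactly balanced, difference 0.6 SD):

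| R2 (assumed) | SE too wide by | t test type I error | Power, t test | Power, adjusted |
|---|---|---|---|---|
| 0 | 1.00 | 5% | 62% | 62% |
| 0.1 | 1.05 | about 4% | 62% | 66% |
| 0.2 | 1.12 | 2.6% | 63% | 71% |
| 0.4 | 1.29 | 1.3% | 64% | 83% |
| 0.5 | 1.41 | 0.7% | 65% | 89% |

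The adjusted model holds its type I error at about 5% throughout. Simulation error is about one percentage point.

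**Difference detectable with 80% power at R2 = 0.4.**
- Planned t test on matched data: critical value x reported SE + 0.842 x true SE = 1.993 x 0.262 + 0.842 x 0.203 = 0.69 SD. Simulation gives 79.3% power at 0.69 and 80.2% at 0.70, so about 0.70 SD.
- Adjusted model: 0.743 x sqrt(0.6) = 0.58 SD, where 0.743 SD is the t test's detectable difference for unmatched groups of 54 and 20.

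**Residual imbalance.** If the groups still differ by 0.3 SD on the matching covariate, the t test's type I error returns to about 5% at R2 = 0.2, 0.4 and 0.5. The bias from the imbalance offsets the conservatism. The two problems act in opposite directions, and the table covers only the balanced case.

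**Would a paired t test do?** With 21 one-to-one pairs, 57 - 21 = 36 fatigued patients are dropped. The paired SE is SD x sqrt(2(1 - rho)/21). It falls below the unpaired SE for 57 v 21 (0.255 SD) only if the within-pair correlation rho exceeds 1 - 0.255^2 x 21/2, about 0.32.

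**The case against.** The strongest reply is that the planned test remains valid. The Power calculation section speaks of a matched group, no pairs are defined, an unpaired test is common in that setting, and with 57 v 21 a plain paired test is not a natural choice. All of this stands: the point concerns efficiency. A condensed article may also leave covariate detail to a fuller plan. That carries less weight here, because the article itself names the test and the test does not use the design that it describes.

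It is also fair to say that the size of the loss is unknown. At R2 = 0 nothing is lost, and at 0.1 the gain is 4 points of power. That age and sex matter for exercise capacity has one support in the text, the sex-specific exercise protocol ("Patients will cycle with an increased workload of 10 Watt/min for women and 20 Watt/min for men"). The article does not show how far the matching factors explain central activation failure, conduction velocity, metabolite levels or brain volumes.

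Some stronger readings are tempting but not supported:
- A reader might infer excess false positives. Under balanced groups the t test's error rate is at or below 5%.
- A reader might set 0.74 SD against 0.58 SD as the gain. The 0.74 applies to unmatched groups; on matched data at R2 = 0.4 the gain is from about 0.70 to 0.58 SD.
- A reader might take this as the only analysis bearing on physiological characteristics. The section on fatigue and psychosocial measures also relates daily fatigue to these measures, and the Statistical analysis section tests change within and between arms.
- A reader might want current hormonal therapy or intracranial volume as required covariates. These are separate questions, and the article does not show that either is recorded for this purpose.

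**Conclusion.** The point holds as an inefficiency in a stated analysis, of minor to moderate severity. The design matches on three factors, and the named test for the matched comparison uses none of them. Where the factors explain outcome variance and the groups are balanced, the reported standard error is too wide by about 1/sqrt(1-R2). At a true difference of 0.6 SD the power forgone is nil at R2 = 0, 4 points at 0.1, 8 at 0.2, 19 at 0.4 and 24 at 0.5. These figures rest on the assumed R2, the assumed difference and exact balance. The direction is firm under balance; the size will differ by outcome and cannot be fixed from the article. Any imbalance left after matching goes uncorrected under the plan.

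**What to change.** For the fatigued v non-fatigued baseline comparison, replace the independent-samples t tests with a linear model of each outcome on group, age, sex and previous cancer treatment. Include all evaluable patients, and report the adjusted mean difference with its 95% CI. State whether matching is individual or by group; if individual sets are formed, add the set as a random effect. Do not switch to a paired t test on 21 pairs.

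The cost is a change of wording and a few of the 54 + 20 - 2 = 72 error degrees of freedom. The three covariates have to be known for the matching to be carried out, so no new measurement is needed for them.

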### Randomization and intervention

As shown in Figure 1, severely fatigued patients will be randomized to either the intervention group (75%) or the control group (25%). Randomization will take place per patient. Patients randomized to the intervention group will be treated with CBT for PCF, as described previously.[14] The treatment consists of 12–14 individual sessions in six months. Patients randomized to the control group will be treated with CBT after six months.

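### The only covariate rule for the randomised comparison lets chance baseline differences between about 30 and 10 patients choose the model, instead of fixing each outcome's own baseline as a covariate

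*Protocol article*

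**What the plan says.** The protocol article's Statistical analysis section sets out the randomised comparison in two sentences. The first is the covariate rule: "Baseline differences between the therapy and waiting list condition are entered as covariates in further analyses". The second gives the model, which compares the two randomised groups "on the change in outcome measures from baseline to 6 months later will be calculated with analyses of covariance (ANCOVA").

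No covariate is named, neither the outcome's own baseline nor any other. No criterion says what counts as a baseline difference, whether a test, a size or a judgement. No other section adds a covariate. Age, sex and previous treatment appear under Study population only as matching factors for the non-fatigued comparison group.

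The Power calculation section gives the evaluable numbers: "Based on 30 patients in the CBT condition and 10 patients in the waiting list condition".

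**The concern.** In a randomised comparison, any baseline difference between arms is due to chance. A covariate earns its place by predicting the outcome, and that can be decided before the data are seen. A rule driven by observed differences has three weaknesses here.

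- **The model is not fixed.** The abstract lists several primary domains (fatigue severity, central and peripheral fatigue, brain measures, physical condition and activity). Each could end up with a different covariate set, and the undefined criterion leaves room for choice after the data are seen.
- **Imbalance can be missed.** With 10 controls, a sizeable baseline gap can fail to register as a difference and then goes uncorrected.
- **Precision can be lost.** If own baseline does not appear to differ, a literal reading leaves an unadjusted change score. That over-corrects for baseline when the correlation with follow-up is modest.

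At stake are the precision and the pre-specification of the trial's only randomised comparison.

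**Working it through.** **Inputs from the protocol article.** 30 CBT and 10 waiting-list evaluable patients, response 67% v at most 10%, power at least 80% (Power calculation). The arm sizes are consistent with the stated losses: 57 × 0.80 × 0.95 = 43.3 evaluable, which at 3:1 is 32.5 and 10.8.

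**Assumptions, not in the document.** Two-sided 5% level, a p<0.05 screen as the meaning of a baseline difference, baseline/follow-up correlation r of 0.3, 0.5 or 0.7, equal SDs at both times, and a 0.8 SD effect for the illustration.

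**1. The plan's own figure.** For 67% v 10% with 30 v 10:
- pooled proportion = (30×0.67 + 10×0.10)/40 = 0.5275
- null SE = √[0.5275×0.4725×(1/30+1/10)] = 0.182
- alternative SE = √[0.67×0.33/30 + 0.10×0.90/10] = 0.128
- z = (0.57 − 1.96×0.182)/0.128 ≈ 1.66, so power is about 95%

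Fisher's exact test gives 89%. At least 80% is confirmed. This calculation uses response proportions, so the covariate rule does not touch it.

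**2. How often the rule would act.** Under a p<0.05 screen, own baseline enters in about 5% of trials, so about 95% would analyse change without it. With, say, 11 independent candidates, the chance that at least one enters is 1 − 0.95^11 = 43%.

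**3. Imbalance that escapes.** The SE of a baseline difference is √(1/30+1/10) = 0.365 SD. The screen passes over gaps up to about 2.02 × 0.365 = 0.74 SD. An unadjusted change score is then shifted by (1−r) × gap, at most 0.52, 0.37 and 0.22 SD at r = 0.3, 0.5 and 0.7.

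**4. Precision.** With equal SDs, the variance is 2(1−r) for change and 1−r² for ANCOVA on own baseline. The ratio is (1+r)/2 = 0.65, 0.75, 0.85. To match, unadjusted change would need 2/(1+r) − 1 = 54%, 33%, 18% more patients (large-sample formula).

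**5. Simulated power, 30 v 10, effect 0.8 SD.**

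| r | Include own baseline only if p<0.05 | Always include own baseline |
|---|---|---|
| 0.3 | about 44% | about 60% |
| 0.5 | about 58% | about 68% |
| 0.7 | about 79% | about 84% |

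With no effect, the selective rule rejects in about 4.1% to 4.7% of trials, so false positives are not inflated.

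**6. Where the loss shrinks.**
- *Effect planned for CIS-fatigue.* Under a normal model with equal SDs, 67% v 10% below the cut-off corresponds to 0.44 + 1.28 = 1.72 SD. Power is then about 98% v 99.7% at r=0.3, and above 99.5% for both at r=0.5 and 0.7. The loss is at most about 2 points.
- *Entry at CIS-fatigue ≥35.* Selecting on baseline leaves the regression slope and residual variance unchanged and reduces baseline variance. The change-score penalty is (1−slope)² × baseline variance, so it falls. If the top 30% are selected (an assumption; the Background gives a prevalence of 19 to 39%), baseline variance drops to about 0.26. ANCOVA's advantage falls from 35%, 25% and 15% to about 12.5%, 8% and 4.5% (unrestricted r = 0.3, 0.5, 0.7). Simulated at 30 v 10, it is lower still, about 10%, 6% and 2%.
- *Very high r.* At 30 v 10 the cost of estimating the slope offsets the gain. The two variances are about equal at r=0.95, and ANCOVA has no advantage above that.

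**The case against.** The strongest objection is that the article calls the analysis ANCOVA on change, without condition. An ANCOVA with no covariate is not an ANCOVA, so own baseline may have been meant throughout, with imbalanced variables added to it. The text does not exclude this. Under that reading there is no loss from omitting own baseline, because change and follow-up give the same arm effect once baseline is in the model. The article is also condensed, and a full covariate list commonly sits in the analysis plan. In addition, the p<0.05 screen and the 0.8 SD effect are not the protocol's.

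Much of this stands, and it limits the size of the point. It does not remove it. The article does not leave the covariates open: it states a rule, and the rule selects by observed difference. Even on the generous reading, the additional covariates are still chosen from the data.

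Four stronger conclusions that a reader might draw are not supported:

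- **False positives are inflated.** They are not. The selective rule is slightly conservative, and a change-score comparison is unbiased over randomisation.
- **The 80% power claim fails.** It reproduces, and it rests on response proportions.
- **CIS-fatigue suffers most because of the entry cut-off.** The effect runs the other way: selection on baseline narrows the gap between the two analyses.
- **Adjustment gains for every r below 1.** With 10 controls it does not, once r reaches about 0.95.

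**Conclusion.** The point holds as one of pre-specification and efficiency. The written rule makes the model for the randomised comparison depend on chance differences between about 30 and 10 patients, possibly differently for each outcome. On a literal reading it usually leaves out the most useful covariate.

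The power cost on that reading is roughly 16, 10 and 5 percentage points at r = 0.3, 0.5 and 0.7. These are illustrations under the listed assumptions, not estimates for this trial: the document gives no correlation for any outcome, and no effect size for any outcome except fatigue response. For CIS-fatigue at the planned effect, the loss is at most about 2 points. For the neurophysiological, imaging and fitness outcomes it could be larger, but the document does not allow it to be sized. If own baseline was always intended, the loss from omitting it is nil and only the data-driven choice of additional covariates remains.

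**What to change.** Replace the covariate sentence with wording such as:

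> For each outcome, the 6-month value (or the change from baseline) is analysed by ANCOVA with randomised arm and the baseline value of that same outcome as a fixed covariate. Any further covariates are named in advance, and none is chosen from observed baseline differences between the arms.

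Baseline comparisons of the randomised arms then stay descriptive. Age and sex may be named as further covariates, but nothing here requires them.

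The cost is one sentence in the protocol or analysis plan and one degree of freedom per model. No new data are needed, since the outcomes are already measured at baseline.
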